#### Data collection

*Contextual information* will be collected at baseline on factors that might moderate feasibility or benefits. This will include demographic information (self-report) and clinical data from the participant’s electronic patient record, including their score on the Expanded Disability Status Scale [43] (Recommendation 20), which is assessed by a neurologist at each clinic visit (at least annually in stable disease and more frequently where clinically indicated). For participants recruited at a neurologist appointment, this will have been performed at that appointment. As hand function can be compromised in MS [44] and could affect CIRCuiTS™ MS’ feasibility and acceptability (Recommendation 20), the MAM-36 will also be administered. This is a self-report measure of ability to perform 36 one- or two-handed tasks, with higher total scores indicating better function.

IQ will be assessed with vocabulary and matrix reasoning tests from the Wechsler Abbreviated Scale of Intelligence, Second Edition (WASI-II) [45] and premorbid IQ with the Wechsler Test of Adult Reading (WTAR) [46].

Therapists will record the current temperature at the participant’s location at each session according to data issued by the Met Office (https://www.metoffice.gov.uk/) (Recommendation 20).

Primary outcome: *Trial feasibility and acceptability* will be evaluated quantitatively using Go/No-Go thresholds (Table 3), including self-reported acceptability on the Theoretical Framework of Acceptability (TFA) questionnaire [47], a measure of healthcare intervention acceptability administered at Assessment 3. Acceptability and perceived burden will be further explored through qualitative analysis of semi-structured one-on-one interviews with a trained researcher at Assessment 3.

**Table 3 Tab3:** Feasibility outcome measures and decision rules

Measure	Operationalisation	‘Go’ criterion	‘No-Go’ criterion
Reach			
Recruitment	% planned sample size recruited	Enrolling ≥ 80% of the planned sample size	
Ethnic enrolment diversity	% sample belonging to most common ethnicity	< 75% participants of a single ethnicity^1^	
Gender enrolment diversity	% participants identifying as male and female	< 50% difference between those identifying as men and women^2^	
Retention			
Completion rate	% completing 27-week outcomes	≥ 50% participants finally retained at 27 weeks	
Midpoint retention	% completing 14-week outcomes	≥ 70% participants retained 14 weeks	
Dropout	% enrolled participants who drop out	< 10% dropout due to adverse events directly related to the intervention	
Safety			
Serious adverse events	Number of serious adverse events (SAEs) reported	No SAEs directly related to the intervention reported	An SAE directly related to the intervention
Manageability of adverse events	Number of adverse events that cause the study to be halted reported	Only mild to moderately severe adverse events that are managed without halting the study	Any adverse event that poses a significant risk to participant safety and cannot be mitigated
Data Integrity			
Data completeness	Overall percentage outcome data complete	≥ 50% completeness in outcome data^3^	
Specific measure completeness	Percentage outcome data complete per measure	≥ 50% complete indicates that measure is feasible	
Operational feasibility	Number of significant operational issues that cannot be resolved	Only resolvable operational issues arise	Significant, unresolvable operational issues arise, e.g. persistent software problems or insufficient staff for the study
Intervention feasibility			
Adherence:	% attending therapy sessions	> 50% participants adherent	
Independent sessions	% attending independent sessions	> 50% participants adherent	
Measure acceptability	% who complete demographic questions	Questions for which ≤ 50% select ‘Prefer not to say’ will be considered feasible	Questions for which > 50% select ‘Prefer not to say’ will not be considered feasible
Acceptability	Mean score on the general acceptability item of the Theoretical Framework of Acceptability [47]	Mean score of > 2.5	

^1^Based on a UK average of 82% White but larger non-White representation in South London

^2^Based on a 1:3 ratio in UK population with MS

^3^Measured as the percentage of measures intended to be collected that were successfully collected across participants

A decision to progress to a larger trial will be based primarily on feasibility of recruitment; if recruitment is not feasible, a definitive trial would not be possible. If this Go criterion is met, decisions regarding progression and the need for substantial amendments to the study design will be informed by the remaining Go/No-Go criteria and findings from the exit interviews. Measures that fail to meet criteria for completeness and acceptability will be omitted or substituted in any future trial.

Secondary outcomes: Changes following treatment will be measured with the following instruments.*Personal recovery* will be assessed with the Goal Attainment Scale (GAS) [48], as it is a personalised measure but scores are on a similar scale, so achievement of goals can be assessed across the group. As individuals with MS will have different types of goals, this was thought to capture that variability and be preferable to participants (Recommendation 19).*Cognitive function* will be assessed (Recommendation 19) through tests of attention, processing speed, working memory, and executive function, following prior work on cognitive vulnerabilities in MS [49–51]. These cognitive domains will be measured on three tests incorporated into the Brief International Cognitive Assessment for Multiple Sclerosis (BICAMS) [50]: (i) Symbol Digit Modalities Test (SDMT) [52], a measure of processing speed and attention, (ii) the Brief Visuospatial Memory Test-Revised (BVMT-R) [53] for visuospatial working memory capacity, and (iii) the California Verbal Learning Test-Second Edition (CVLT-II) [54], for verbal working memory capacity. The BVMT-R was selected for this study for its brevity, reliability, and sensitivity to cognitive changes associated with MS. The oral version of the SDMT will be used to reduce motor demands [55] (Recommendation 20). As this battery does not test executive function, it will be supplemented by the Digit Span test from the WAIS-IV [56] and the Controlled Oral Word Association Test (COWAT) [57]. The participant must perform operations in working memory for the backwards and sequential parts of the Digit Span and apply cognitive flexibility and inhibitory control in the COWAT, all of which are aspects of executive function. Both measures show good test–retest reliability and convergent validity. In addition to these formal tests, we also want to assess another aspect of perceived benefits, the awareness of experiencing cognitive problems, as this may affect the adherence to therapy. This will be assessed using the Measure of Insight into Cognition (MIC) [58].*Mood* is important in MS, and there was some concern that mental health issues may emerge as the participant becomes more aware of their cognitive difficulties (Recommendation 21). Although the therapy and therapist emphasise building on strengths, the trial will exclude potential participants who have moderate to severe depression in case of potential exacerbation during therapy. Mood will be assessed using the PHQ-9 [38], which is a widely used short, self-administered tool that has been validated as a screening tool in MS [59]. Those exceeding a score of 9 (moderate to severe depression) will be excluded from the study. Anxiety will also be measured, as it may affect adherence to the treatment or trial protocol. It will be assessed on the short, self-report Generalised Anxiety Disorder Scale (GAD-7) [60], a tool validated in MS [61] where a higher total score indicates greater anxiety severity.*Fatigue* will be assessed (Recommendation 19) with the Fatigue Severity Scale (FSS) [62], a common measure of the impact of fatigue on daily life that has been validated in MS (e.g. [63, 64]). The total score is the average of the item scores, with higher scores indicating greater severity and impact.*General ability to carry out everyday activities* will be assessed (Recommendation 19) using the Work and Social Adjustment Scale (WSAS) [65], comprising questions about how the participant’s condition, in this case MS, affects their daily life.

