#### Aim and design

This trial will determine whether delivering CIRCuiTS™ cognitive remediation therapy to people with MS experiencing cognitive difficulties is feasible and acceptable.

The design is a randomised, parallel-group, waitlist-controlled feasibility trial (Fig. 1). Participants will be randomly assigned, with equal probability, to receive 12 weeks of cognitive remediation either immediately (immediate treatment group) or after 13 weeks’ wait (delayed treatment group). This design offers fair access for all participants to a treatment that has been shown to be effective in other conditions and is anticipated to offer numerous benefits to people with MS (Recommendation 19). The waiting time for the delayed treatment was also acceptable and likely to encourage engagement throughout study assessments (PPI lead design input). At the end of the trial (week 27) there will also be an exit interview covering topics like acceptability of the trial procedures and the treatment provided. As well as the primary outcomes of feasibility and acceptability, measures to be used in a further trial including recovery measures and cognition will be assessed at weeks 0, 14 and 27 (see Table 2). Outcome assessors will be blind to group assignments to reduce measurement bias. In case of unblinding, a different, blinded assessor will complete all further assessments. Each assessment can be split over more than one session in case of fatigue.

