##### Aim 1: Feasibility and acceptability

Feasibility and quantitative aspects of acceptability will be measured quantitatively through evaluating trial performance against the Go/No-Go criteria (Table 3).

Acceptability will be explored further through framework analysis of qualitative data [66] from participant interviews using NVivo version 14 [35]. A researcher will check the transcriptions then review and index the data. A thematic framework followed by a summary in a framework matrix will be created by two independent researchers. Following good research practice [27] and a commitment to PPI, participants will be asked to provide feedback on the results of this analysis as part of member checking, which will be synthesised into reports disseminating the research.

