##### Aim 2: Potential benefits

Quantitative outcome data will be analysed on an intention-to-treat basis, with all randomised participants included regardless of adherence. The focus will be on descriptive statistics and 95% confidence intervals to assess the likely range of treatment effects. The GAS T-score will be evaluated using a linear mixed model.

Means and standard deviations for scores on measures of the secondary outcomes will be calculated at each assessment point for both groups and for groupwise within-subject change in score across assessment points, and the distribution of scores will be summarised to assess normality.

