##### Sample size

Twenty-four participants will be recruited. Drawing on prior experience, this number is considered sufficient to estimate key feasibility outcomes (e.g. recruitment and dropout rates), meaningfully assess the practical challenges that might arise from participation (Recommendation 20), and recruit a range of participants with different characteristics. It also follows recommendations to include at least 12 participants per pilot group (24 in total) to adequately estimate the variability of outcome parameters in a larger definitive trial [67]. This target sample size was also considered feasible by the recruiting site within the planned recruitment period.

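### The related-dropout Go in Table 3 is computed over everyone enrolled, so people lost before therapy starts dilute the rate and can turn a not-Go into a Go.

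*Protocol article*

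**What the plan says.** The section Aim 1: Feasibility and acceptability makes Table 3 the yardstick for the primary outcome: "Feasibility and quantitative aspects of acceptability will be measured quantitatively through evaluating trial performance against the Go/No-Go criteria (Table 3").

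Two rows concern harm attributed to the intervention:

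- **Dropout** (under Retention). The operationalisation column defines the measure as a percentage of enrolled participants. The Go is "< 10% dropout due to adverse events directly related to the intervention". The No-Go cell is empty.
- **Serious adverse events** (under Safety). The measure is a number of events. The Go is "No SAEs directly related to the intervention reported", and one related SAE is the No-Go.

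Safety has a further row, on whether adverse events can be managed without halting the study.

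Under Sample size: "Twenty-four participants will be recruited". Under Aim and design: "Participants will be randomly assigned, with equal probability", either to immediate therapy or to therapy "after 13 weeks’ wait (delayed treatment group"). Table 3 also sets a recruitment Go of at least 80% of the planned sample and retention Gos of at least 70% at week 14 and at least 50% at week 27.

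**The concern.** A dropout caused by the intervention can happen only in someone who has begun it. In a waitlist design, enrolled and exposed are different groups. Anyone in the delayed arm who leaves during the wait is enrolled but never exposed, and adds one to the denominator with no possibility of adding to the numerator. The same holds for anyone in the immediate arm who withdraws before the first session.

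The bias has one direction: the more people are lost before therapy, the lower the related-dropout percentage looks. A feasibility problem (waitlist attrition) thus improves the score on a tolerability criterion. What is at stake is whether the row is reported as met when, among those who received therapy, the rate was at or above the protocol's own 10% limit.

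**Working it through.** **Inputs, all from the protocol article.** Planned sample 24 (Sample size). Recruitment Go at least 80%: 0.80 × 24 = 19.2, so at least 20 enrolled. Dropout Go below 10% of enrolled, and week-14 retention Go at least 70% (both Table 3). Delayed therapy after a 13-week wait (Aim and design). I take the retention percentages to be of those enrolled.

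**Step 1. What the row allows as written.** With 24 enrolled, 2/24 = 8.3% is a Go and 3/24 = 12.5% is not. With 20 enrolled, 1/20 = 5.0% is a Go and 2/20 = 10.0% is not.

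**Step 2. When the denominator changes the result.** With two related dropouts, the rate among those treated reaches 10% when 2/(number treated) ≥ 0.10, that is, when 20 or fewer are treated.

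| Enrolled | 2 / enrolled | Row as written | Never started, at least | 2 / treated | Row among treated |
|---|---|---|---|---|---|
| 24 | 8.3% | Go | 4 | 2/20 = 10.0% | not Go |
| 23 | 8.7% | Go | 3 | 2/20 = 10.0% | not Go |
| 22 | 9.1% | Go | 2 | 2/20 = 10.0% | not Go |
| 21 | 9.5% | Go | 1 | 2/20 = 10.0% | not Go |
| 20 | 10.0% | not Go | – | – | not Go |

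Three related dropouts exceed 10% at any of these sizes. One would need 10 or fewer treated, which means at least 14 of 24 never starting. The reversal is therefore confined to exactly two related dropouts.

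**Step 3. Is this compatible with the retention Gos?** Take the least favourable timing: the never-starters and both related dropouts are all gone by week 14. In each of the first four table rows, 18 people remain.

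- 24 enrolled: 18/24 = 75.0%. The Go needs 17, since 0.70 × 24 = 16.8.
- 23 enrolled: 18/23 = 78.3%.
- 22 enrolled: 18/22 = 81.8%.
- 21 enrolled: 18/21 = 85.7%.

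All meet 70% at week 14, and all meet 50% at week 27 if nobody else leaves.

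**Step 4. How often it would matter.** The documents give no related-dropout rate, so this step uses assumed rates and independent events. Suppose 24 are enrolled and 20 start. As written, up to 2 dropouts pass; among those treated, only up to 1 passes (1/20 = 5.0%). The two rules disagree when exactly 2 occur: P(X = 2) = 190 × p² × (1 − p)^18.

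| Assumed rate p among treated | Go as written, P(X ≤ 2) | Go among treated, P(X ≤ 1) | Difference |
|---|---|---|---|
| 5% | 0.925 | 0.736 | 0.189 |
| 10% | 0.677 | 0.392 | 0.285 |
| 15% | 0.405 | 0.176 | 0.229 |

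**Step 5. The SAE row.** It is a count with a threshold of zero, so adding or removing event-free people cannot change whether it is met. Only its interpretation depends on the number treated. After 0 events in n, the exact one-sided 95% upper limit is 1 − 0.05^(1/n): 11.7% for n = 24 and 13.9% for n = 20.

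**The case against.** **Enrolled is a declared denominator, and preferring treated is a choice.** It is declared, which is why it can be assessed here and is not a matter left to an unseen analysis plan. But the criterion is about dropout caused by the intervention, and the unexposed are not at risk of that.

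**The reversal is narrow.** This stands. It needs exactly two related dropouts. With 24 enrolled it also needs four people who never start, which is a third of a 12-person delayed arm if all come from there. With 20 enrolled the row already fails.

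**The row does not decide progression.** This stands too. Table 3 gives it no No-Go, and the text below the table puts recruitment first, with the remaining criteria and exit interviews informing the decision.

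**The number treated can be recovered from therapy attendance.** Probably so, which makes the change cheap. It does not correct the rule as fixed.

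**A stronger reading.** A reader might infer that the zero-SAE Go is itself unsound: it has no upper bound and no treated denominator, and a true 5% related-SAE rate would go unseen about 3 times in 10 (0.95^24 = 0.292). The documents do not support that. The 29% follows from 24 people and an assumed 5%; at n = 24 the figure runs from 79% at 1% to 8% at 10%, and no added bound or denominator would change it. The rule is strict, since one related SAE is a No-Go. Safety also has the manageability row, and adverse events go to clinical review and the Steering Committee. The protocol nowhere says that zero events establishes safety. Interval reporting for such counts is commonly left to the full protocol or analysis plan.

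**Conclusion.** The point holds for the dropout row alone. Its denominator includes people who cannot have the event, so losses before therapy lower the percentage and can turn a not-Go into a Go while the retention criteria are met. The smallest number of never-starters that does this is four with 24 enrolled and one with 21, in each case with two related dropouts. If four of 24 never start, the two denominators give different results with probability 0.19 to 0.29 over assumed related-dropout rates of 5% to 15%.

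This rests on reading the Go percentage against the denominator in the same row's operationalisation, and on people who leave before therapy being counted as enrolled, as that wording implies. It is a bias in one stated decision rule with modest consequences. It does not show that the safety criteria are invalid or that the sample size is wrong.

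**What to change.** In Table 3, define the dropout row as the percentage of participants who started therapy and then dropped out because of an adverse event directly related to the intervention. State what counts as starting, for example attending at least one therapy session. Show the number who started beside this row and beside the related-SAE count. Losses before therapy remain captured by the midpoint and completion retention rows.

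The cost is a change of wording and one extra count; no new data or participants are needed. The downside is a slightly less favourable dropout percentage when some people never start.

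Optionally, report the exact one-sided 95% upper limit with the SAE result, for example that 0 of 24 treated excludes only rates above 11.7%. This aids interpretation and does not correct an error. The zero-SAE rule can stay as it is.

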
#### Data management

Any personally identifying information will be stored on a secure server separately from non-identifying information and password protected, with access rights minimised to research team members who need to view it to carry out trial activities. Paper copies will be stored in a locked cabinet.

All assessment data will be stored using a unique numeric participant identifier separately from all personally identifiable information. Standardised test data will be recorded using publisher-provided scoring forms. Self-report measures and summary statistics from standardised tests will be entered by the assessor into the Qualtrics platform. Qualtrics range validation checks will be used to promote data quality. Data verification will be conducted at the midpoint and end of the study by an independent scorer, who will calculate summary statistics for a random 10% sample.

Identifiable data will be stored for 24 months, after which it will be converted to a de-identified format and retained for a further 5 years.

#### Analysis

This analysis plan was developed in collaboration with a statistician at King’s College London.

##### Aim 1: Feasibility and acceptability

Feasibility and quantitative aspects of acceptability will be measured quantitatively through evaluating trial performance against the Go/No-Go criteria (Table 3).

Acceptability will be explored further through framework analysis of qualitative data [66] from participant interviews using NVivo version 14 [35]. A researcher will check the transcriptions then review and index the data. A thematic framework followed by a summary in a framework matrix will be created by two independent researchers. Following good research practice [27] and a commitment to PPI, participants will be asked to provide feedback on the results of this analysis as part of member checking, which will be synthesised into reports disseminating the research.

##### Aim 2: Potential benefits

Quantitative outcome data will be analysed on an intention-to-treat basis, with all randomised participants included regardless of adherence. The focus will be on descriptive statistics and 95% confidence intervals to assess the likely range of treatment effects. The GAS T-score will be evaluated using a linear mixed model.

Means and standard deviations for scores on measures of the secondary outcomes will be calculated at each assessment point for both groups and for groupwise within-subject change in score across assessment points, and the distribution of scores will be summarised to assess normality.

##### Sample size

Twenty-four participants will be recruited. Drawing on prior experience, this number is considered sufficient to estimate key feasibility outcomes (e.g. recruitment and dropout rates), meaningfully assess the practical challenges that might arise from participation (Recommendation 20), and recruit a range of participants with different characteristics. It also follows recommendations to include at least 12 participants per pilot group (24 in total) to adequately estimate the variability of outcome parameters in a larger definitive trial [67]. This target sample size was also considered feasible by the recruiting site within the planned recruitment period.

#### Data and trial monitoring

Data and trial monitoring will be carried out by a Steering Committee that includes three academic clinical psychology trialists, a mental health professional, two neurologists and two people with MS. This committee will regularly review study methodology, management, and analysis to ensure the study stays patient-focused and complies with ethical trial procedures. The Chief Investigator oversees the regular monitoring of protocol adherence, consenting procedures, and data quality. Any concerns will be reported to the sponsor.

